### 2.7. Physical activity

To enroll this study, as stated in inclusion criteria, participants needed to be considered inactive (less then 150 min/week of moderate PA or 75 min/week of vigorous PA [34]). This PA level should be maintained throughout the WL and WM phase.

### 2.8. Retention of the participants

All efforts will be made before, during and after the intervention to retain participants in the study, in order to manage costs, equipment, human resources and data colleting time.

#### 2.8.1. Strategies to engage participants, avoid low attendance and dropouts

During the intervention, and throughout the 8 visits to the laboratory for assessment and consultations, participants will be reminded of the importance of adhering to the recommendations, as well as attending appointments. Some flexibility will be taken into consideration, as long as it does not interfere with the study plan/goals. A 1-week adjustment will be considered as an on-time assessment, maintaining the previously defined length of each study phase.

Between the scheduled visits and consultations, additional contacts will be held by phone, following up results and adherence to the dietary plan.

After the intervention phase is over (7^th^ visit), and the 12-month WM phase starts, the research team will remain available to follow-up the participants, with at least one phone/video consultation per month.

#### 2.8.2. Rewards for participation

Participants will not receive any type of financial incentive. Nevertheless, they will benefit from a free nutritional intervention for WL and WM, which includes 8 nutrition appointments and weekly remote follow-up by a certified clinical dietitian for 78 weeks (CER group), or 85 weeks (IER group).

## 3. Measurements

Body weight, body composition and resting energy expenditure (REE) will be collected at 8 different moments, and DXA scans at 5 different moments, as described in Fig 2. Participants will be informed not to take diuretics in the previous 7 days, have alcoholic drinks/coffee in the previous 24 hours, and perform vigorous PA 24-hours prior to the laboratory visits, and to urinate 30 minutes before evaluations [48, 49]. All evaluations will be performed with a minimum 10-hour overnight fast, barefoot and wearing underwear and a disposable vest, to preserve participants comfort.

**Fig 2 pone.0294131.g002:**
[figure not shown]
Schematic description of the study design. Arrows indicate points for measurements. A—body weight, body composition using bioimpedance analysis (BIA), resting energy expenditure (REE), physical activity (PA) using accelerometry, and calculation of daily energy requirements (DER). B—body composition using Dual-Energy X-ray Absorptiometry (DXA). C—determination of plasma hormones (cortisol, insulin, leptin, thyroid free T3 and T4). *—phone/video contact with research team.

### 3.1 Body composition

#### 3.1.1. Anthropometry

Anthropometry will consider the procedures and recommendations described in ISAK guidelines [50]. Weight and height will be determined using a digital scale with a stadiometer Seca 704s, with 0,1 kg and 0,1 cm intervals (Seca, Hamburg, Germany). Body mass index (BMI) will be calculated using the formula [weight (kg)/height^2^(m^2^)] and the cut-off points of the World Health Organization (WHO) will be used [51].

#### 3.1.2. Dual-Energy X-ray Absorptiometry

In order to assess body composition stores–Fat Mass (FM) and Fat-Free Mass (FFM), a whole-body dual energy X-ray absorptiometry (DXA) scan (Hologic Explorer-W, Waltham, USA) will be used. All the assessments will be performed by the same investigator. Total abdominal fat, which includes intra-abdominal fat plus subcutaneous fat, will be distinguished by identifying a specific region of interest (ROI) within the analysis program. Specific DXA ROIs for abdominal regional fat will be defined as follows: from ROI 1, the upper edge of the second lumbar vertebra (approximately 10 cm above the L4 to L5) to above the iliac crest and laterally encompasses the entire breadth of the abdomen, thus determining total abdominal fat mass [52].

#### 3.1.3. Bioimpedance analysis (BIA)

Bioimpedance analysis will be performed using BIA-101 BIVA PRO (Akern srl, Florence, Italy). Before the test, subjects will be instructed to lie in a supine position with their arms and legs abducted at a 45 angle for 10 min [53]. Four electrodes will be placed on the dorsal surfaces of the right foot and ankle, as well as the right wrist and hand.

This equipment will measure the resistance (Rz) and reactance (Xc) using a 250 mA alternating current at 50 kHz ± 1%. Calibration will happen every morning according to be manufacturer instructions. Bioelectrical phase angle will be calculated as the tangent arc of Xc/R x 180º/ π. Vectorial analysis of bioimpedance will use BIVA method, normalizing R and Xc for height in meters. FM and FFM percentage will be determined using Bodygram^®^ software (AkernSrl., Florence, Italy) [54].

### 3.2. Resting energy expenditure

REE will be determined using indirect calorimetry COSMED Fitmate (Cosmed, Rome, Italy) using a face mask. Fitmate is a metabolic analyzer designed for measurement of oxygen consumption and EE during rest and exercise. It uses a turbine flowmeter for measuring ventilation and a galvanic fuel cell oxygen sensor for analyzing the fraction of oxygen in expired gases. REE is calculated from oxygen consumption, at a fixed respiratory quotient of 0.85, and estimated grams of urinary nitrogen using a modified Weir equation [55, 56].

The metabolic analyzer will be calibrated in the morning before testing, using a pumping gas with 3 L calibration syringe through the flow meter, according to the manufacturer’s recommendations. The test will be performed early morning (8 a.m. to 11 a.m.), after a minimum 10h-overnight fast. Individuals will be advised to reduce PA the most until the test. All measurements will happen in a thermic neutral environment (approximately 22ºC and humidity between 40–50%) [53], a quiet and dimly lit room, in semi-recumbent position [55]. During the test, participants will be asked to relax and keep immobile, without doing any activities, such as fidgeting, reading, listening to music, talking, nor falling asleep [57]. Rest duration will be 15 minutes, followed by a 30-minute test duration, ignoring the first 10 minutes [58]. Fitmate steady state is achieved when the CV in VO2 is <10% during the 30-minute measurement.

#### 3.2.1. Adaptive thermogenesis

The REE will be predicted (pREE) through linear regression analysis, with the baseline measured REE as a dependent variable, and FM (kg) and FFM (kg) as independent variables. The predictive equation will be used to assess pREE at each time point, using the FM and FFM values of the respective time.

Adaptive thermogenesis (AT) will be assessed by the following equation:

$$\begin{array}{ll} \text{AT}\left(\text{kcal/d}\right) & =\left(\text{mREE}\;\text{at}\;\text{the}\;\text{end}\;\text{of}\;\text{the}\;\text{intervention}–\text{pREE}\;\text{at}\;\text{the}\;\text{end}\;\text{of}\;\text{the}\;\text{intervention}\right)\\ & –\left(\text{mREE}\;\text{baseline}–\text{pREE}\;\text{baseline}\right), \end{array}$$

where negative values will indicate a lower-than-expected REE due to body composition changes [59].

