**Methods:**

Seventy-four women with obesity and inactive (20–45 y) will be randomized to 16 weeks of CER or IER (8x2 weeks of energy restriction interspersed with 7x1 week in energy balance). Both groups will start with 2 weeks in energy balance before energy restriction, followed by 16 weeks in energy restriction, then 8 weeks in energy balance and finally a 12-month weight maintenance phase. Primary outcomes are changes in fat-mass and adaptive thermogenesis after weight loss and weight maintenance. Secondary outcomes include weight loss, fat-free mass preservation, alterations in energy expenditure components, and changes in hormones (thyroid function, insulin, leptin, and cortisol).

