### 3.5. Statistics

Statistical analysis will be performed using SPSS statistics software version 29.0, 2022 (SPSS Inc., an IBM Company, Chicago IL, USA), with a statistical significance set at p<0.05 (2-tailed).

Descriptive statistics will be calculated (mean, standard deviation, and range). Linear mixed models will be used to assess outcomes for the impact of group, time and group*time interaction, including the randomized group (control vs intervention group) and time (baseline at the 2-week EB, at the start and every 4-week of ER intervention phase, at the start and at the end of the 8-week post-diet EB phase, and at the end of WM phase) as fixed effects. When necessary, adjustments for confounding variables (covariates) will be considered. The covariance matrix for repeated measures within subjects over time will be modelled as unstructured or, if necessary, compound symmetry. The normality of model residual distributions will be examined graphically and with the Kolmogorov-Smirnov test. Difference-in-differences between IER and CER throughout time will be assessed by performing contrasts [Difference-in-differences (DiD)], calculated as the difference between changes for IER (Difference_IER = T2 -T1) and changes for CER (Difference_CER = Time2 –Time1): DiD = (Difference_IER)–(Difference_CER).

All analysis will be intention-to-treat, including data from all the participants who will assign in this study. Sensitivity analyses will be carried out for some variables of interest, by using single imputation of missing data to predict missing outcomes from demographics and baseline measures.

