## 4. Discussion

This RCT aims primarily to evaluate the effects of an IER, interspersing 14 days of ER with 7 days of EB, on body composition (body weight, FM and FFM), and more specifically on AT, during WL and WM phase. It also aims to understand whether participants from both groups (IER and CER) will successfully maintain their WL 12 months after completion of the intervention.

Secondary objectives of this study are the following: (i) to compare the effects of IER and CER on WL, FM loss, and preservation of FFM and REE during the intervention phase; (ii) to determine which group is more successful in the 12-month WM phase and in improving body composition profile (higher FM loss with best preservation of FFM); (iii) to analyze if AT is maintained during WM phase; (iv) to analyze the impact of AT in WM phase, regarding the hormonal adaptation (plasma hormones: cortisol, insulin, leptin, thyroid free T3 and T4).

A 5% WL has been pointed out to be enough to improve metabolic parameters (glycemic measures and triglycerides, blood pressure, HDL and LDL cholesterol) and is currently a standard goal in WL interventions [65]. Nevertheless, a greater reduction of 10% or more can lead to maximal health benefits, reducing many of the comorbidities associated with obesity [66, 67]. In fact, according to Wing and Hill [68], successful WL maintainers should be defined as “individuals who have intentionally lost at least 10% of their body weight and kept if off at least 1 year”. With The BREAK Study we expect to find a clinically significant weight loss [69] of 10% in both groups, considering the length of the ER intervention, and the magnitude of ER [70].

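### Standard errors for adaptive thermogenesis within an arm leave out the sampling error of the baseline REE equation, so claims that AT is present are moderately anti-conservative; the IER–CER contrast is little affected

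*Protocol article*

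**What the plan says.** In section 3.2.1, predicted REE comes from a linear regression fitted "with the baseline measured REE as a dependent variable, and FM (kg) and FFM (kg) as independent variables". The same section then states: "The predictive equation will be used to assess pREE at each time point, using the FM and FFM values of the respective time". AT is measured minus predicted REE at follow-up, less the same quantity at baseline, and a negative value means REE is lower than body composition explains.

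The abstract makes AT a primary outcome: "Primary outcomes are changes in fat-mass and adaptive thermogenesis after weight loss and weight maintenance". Section 3.5 sets out the analysis: "Linear mixed models will be used to assess outcomes for the impact of group, time and group*time interaction". The contrast it names is between arms: "Difference-in-differences between IER and CER throughout time will be assessed by performing contrasts". Section 4 adds a question about the course of AT over time, as a secondary objective: "to analyze if AT is maintained during WM phase".

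Section 3.5.1 sizes the trial on fat mass: 26 women per group, 74 recruited after allowing for 30% dropout. The article gives no SD, standard error or power for AT.

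**The concern.** Predicted REE is not a known quantity. Its FM and FFM slopes are estimated from at most 74 women. When an arm loses fat, each woman's predicted REE moves by slope × change, so any error in the slopes shifts the mean AT of the whole arm in one direction. Analysing more women at follow-up does not reduce it. A mixed model that takes AT as an observed outcome sees only the scatter of AT between women and leaves this shared part out.

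At stake are statements about AT relative to baseline within an arm: that it is present or absent after weight loss, or still present at 12 months. The introduction says that the literature disagrees on whether AT exists after weight stabilisation. It also motivates the trial by a study in men that reported AT in the continuous arm only, at about 209 kJ/d. A false finding of AT in one arm would bear directly on that dispute.

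**Working it through.** **The plan's own figures.** There is none for AT. The numbers of women come from section 3.5.1. With effect size 0.93, a one-sided 5% level and 26 per group, power is 0.952, so 26 is reproduced; 52/0.70 = 74.3 gives the 74 recruited. Whether a one-sided size suits the two-tailed analysis is a separate matter. Here 26 and 74 serve only as sample sizes.

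**Formula.** The intercept cancels, so for each woman AT = change in measured REE − b̂ × change in (FM, FFM). For an arm with n women and mean change d,

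Var(mean AT) = 2·s_w²/n + d′V(b̂)d.

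Here s_w is the within-woman SD of REE. The first term is what a model of AT as data reports; the second is left out. With one pooled equation from N women,

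d′V(b̂)d ≈ (s_b² + s_w²)/(N − 1) × q, with q = (z₁² − 2r·z₁z₂ + z₂²)/(1 − r²).

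z₁ and z₂ are the mean changes in FM and FFM divided by their SDs, r is the FM–FFM correlation, and s_b is the between-woman residual SD. If true AT is zero, the actual level of the nominal 5% test is P(|t₂₅| > 2.060 × reported SE/full SE).

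**Inputs.** From the protocol: N = 74, n = 26, two-sided 5%. Everything else is assumed. Setting A: SD of FM 7 kg and of FFM 5.5 kg, r = 0.5, s_b = 110, s_w = 70 kcal/d, FFM loss 2 kg. Setting B (mild): SD of FM 8 kg and of FFM 5.5 kg, r = 0.3, s_b = s_w = 80 kcal/d, FFM loss 1.5 kg.

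For fat loss, section 4 expects 10% of body weight. At BMI 35 and height 1.55–1.70 m (heights assumed) weight is 84.1–101.2 kg, so 8.4–10.1 kg is lost. With 75–85% of that as fat (assumed), fat loss is 6.3–8.6 kg.

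**Setting A, 8 kg.**
- Reported variance: 2 × 4,900/26 = 376.9, SE 19.4 kcal/d.
- z₁ = 8/7 = 1.143 and z₂ = 2/5.5 = 0.364, so q = (1.306 − 0.416 + 0.132)/0.75 = 1.364.
- Omitted variance: 17,000/73 × 1.364 = 317.6.
- Full SE: √(376.9 + 317.6) = 26.4 kcal/d.
- Level: P(|t₂₅| > 2.060 × 0.737 = 1.517) = 14%.

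| Within-arm AT against zero | Reported SE | Full SE | Actual level |
|---|---|---|---|
| B, 6.3 kg | 22.2 | 24.5 | 7% |
| A, 6 kg | 19.4 | 23.4 | 10% |
| A, 8 kg | 19.4 | 26.4 | 14% |
| A, 10 kg | 19.4 | 29.8 | 19% |

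Simulated trials with true AT of zero agree: 14.1% at 8 kg and 19.8% at 10 kg with the SDs of setting A, and 7% in the mild setting. With the true slopes known, the simulated level is close to 5%.

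**Effect on a conclusion.** 209 kJ/d is 209/4.184 = 50 kcal/d. In setting A at 8 kg the ratio to the SE is 50/19.4 = 2.58 as reported and 50/26.4 = 1.90 in full, on either side of 2.06.

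**Between arms (setting A).** d becomes the difference in mean change, and the reported variance is 2 × 376.9 = 753.8. With arms 3 kg of fat apart, q = (3/7)²/0.75 = 0.245, the omitted variance is 57.0, and the level is P(|t₅₀| > 2.009 × √(753.8/810.8)) = 5.8%. At 2 kg it is 5.4% and at 4 kg 6.5%.

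**End of intervention to 12 months (setting A).** d is the change between those two visits only. With 2 kg of fat regained the omitted variance is 25.3 against 376.9, and the level is 5.7%. With 4 kg it is 8%.

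**The case against.** The strongest reply is that the trial's main AT question is comparative. The stated aim and the named contrast set IER against CER, and there the shared error largely cancels. This stands. A reader might infer that the primary comparison of AT is invalid; the calculation does not support that, unless the arms end up far apart in fat loss.

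Second, no test of AT against zero within an arm is written out. That is correct. Such inference is implied by the time effect in the model and by the objective on AT during maintenance. That objective, read as a change from end of intervention to 12 months, is close to nominal when regain is small. Read as whether AT relative to baseline is still there, it takes the full inflation.

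Third, the size rests on assumptions. This also stands. A reader might call these tests far too optimistic after 8–10 kg of fat loss, but the protocol states no fat loss, and the 6.3–8.6 kg derived above puts 8–10 kg at or above the top. Over wider assumed SDs the level runs from about 6% to over 40%, so only the direction is certain.

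Fourth, the article condenses a fuller plan that may deal with this. Possibly so. But the article fixes both steps, the plug-in equation and the model, and followed as written they omit the term.

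**Conclusion.** The concern holds for within-arm inference on AT relative to baseline. The omission follows from the definition of AT and needs no simulation. Its size does rest on assumptions: SD of FM 7–8 kg and of FFM 5.5 kg, between-woman residual SD 80–110 and within-woman SD 70–80 kcal/d, a pooled equation from 74 women, and 26 analysed per arm. On these, the nominal 5% test runs at about 7–15% with 6–8 kg of fat lost and about 20% with 10 kg. The IER–CER difference-in-differences (about 5–6%) and the change in AT over the maintenance year with small regain are little affected. Because AT is a primary outcome but its named contrast is nearly sound, the severity is moderate.

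**What to change.** Add to sections 3.2.1 and 3.5: *Confidence intervals and p-values for AT will be obtained by a bootstrap over participants; in each resample the baseline REE equation is refitted, AT is recomputed for every visit, and the mixed model is refitted.* State also that the equation is fitted once to both arms pooled, if that is the intention.

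This keeps the protocol's definition of AT and needs no new data. The cost is a short script and wider within-arm intervals.

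One joint mixed model of measured REE on time-varying FM and FFM with group and time should not be offered as equivalent. It also estimates the slopes from within-woman change during restriction, whereas section 3.2.1 takes them from baseline differences between women only.

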### 3.3. Free-living physical activity and total energy expenditure

PA will be determined using ActiGraph wGT3X-BT accelerometer (ActiGraph, Pensacola FL, USA), which expresses minutes per day spent in different activities. Accelerometers will be placed on the right hip close to the iliac crest, and activated when participants go to the laboratory visit, being used during 7 days. The devices must be used while participants are awake, and will only be asked to be removed during water activities, such as shower and swimming. Participants will be asked to register the time and reason each time they take off the accelerometer. The activation of the devices, download and processing will be held with Actilife software (v.6.9.1).

The cutoff values used for defining PA intensity and the average time at each intensity level (sedentary or light, moderate, hard and very hard PA intensities) will be as follows: sedentary or light: <2689 counts per minute^-1^ (<3.00 METs); moderate: 2690–6166 counts per minute^-1^ (3.00–5.99 METs); hard: 6167–9642 counts per minute^-1^ (6.00–8.99 METs); very hard: >9642 counts per minute^-1^ (>8.99 METs) [60].

Among adults, at least 3–5 days of monitoring are required to estimate usual PA [61], therefore participants will be included if they show a minimum of three valid days of accelerometer data. A valid-day will be defined as having 600 or more minutes (≥ 10 h) of monitor wearing, corresponding to the minimum daily use of the accelerometer.

TDEE will be calculated as the sum of REE, thermic effect of food (TEF) and PA energy expenditure (PAEE) [62]. PAEE data will be collected through accelerometry using Crouter and colleagues’ equations [61, 63, 64].

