Continuous energy restriction (CER), meaning a constant daily energy restriction (ER) according to individual’s energy requirements, is the most common nutritional strategy for WL [20, 21]. However, some concerns have been pointed out to this strategy, since the behavioral, metabolic and endocrine adaptive responses it causes can compromise therapeutic adherence, undermining WL and WM [21–23]. These adaptive responses include an increased drive to eat, a reduced physical activity (PA) or energy cost of PA, a reduced energy expenditure (EE), and hormonal effects that facilitate the accumulation of adipose tissue and loss of lean tissues [24]. ER is associated with a reduction in thyroid hormones secretion (T3 and T4), variations in appetite-regulating hormones (decreased leptin, peptide YY, and increased ghrelin), variations in steroid hormones (increased cortisol), reduced insulin and testosterone, that all together influence EE, satiety and body composition [25, 26]. Simultaneously, some behavioral adaptations as a response to negative EB may occur, such as increasing sedentary behavior and/or decreasing light PA, more consistently observed in diet-only induced WL [26, 27].

Intermittent energy restriction (IER), which consists in interspersing periods of ER with periods of EB (the “refeed” or “diet breaks”), has been suggested as an alternative to CER [22]. The inclusion of periods of neutral EB is expected to attenuate adaptive responses to ER and WL in some regulatory hormones, which play a role in WL, satiety and REE [22, 24].

According to literature, there are 8 randomized clinical trials (RCT) comparing CER with IER in people with overweight/obesity, that achieved EB in the refeeding phases [6, 22, 23, 28–32]. Of these, only three resulted in a greater WL with IER [6, 23, 30]. Variability in study design in these 8 RCT may have contributed to the different findings, favoring IER or not in comparison with CER. The study design differed in the duration of the intervention, the pattern of intermittency (days of ER vs. EB), the severity of calorie restriction, the food provision, the exercise recommendations, the adherence to the intervention, the sample size, and the baseline characteristics of the study population (sex and BMI).

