**Inclusion criteria**
Female sex; BMI 30–39.9 kg/m^2^; Age 20–45 years; Weight stable (less than 5% of weight variation in the past 6 months); Inactive (less then 150 min/week of moderate PA or 75 min/week of vigorous PA [34]); Living in Lisbon metropolitan area; Available to be randomized to any of the trial groups; Willing to commit with the assigned group protocol, and being available for the 8 evaluations.

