According to Byrne and colleagues [6, 25, 71], adaptive responses to ER and WL can be reversed by a 7-to-14-day period of EB after, in adults with overweight or obesity. In “MATADOR” Study, a IER using a 2-week EB periods improved WL efficiency compared with CER, being AT only found in CER group, despite the lower WL and FM loss [6]. In review by Peos and colleagues [21], it was stated that “refeeds” with at least 7 days attenuate the adaptive responses to longer-term periods of ER, potentially by attenuating the reductions in EE. Furthermore, these authors also mentioned that adopting refeed periods in IER may provide a mental break from extended periods of ER, leading to a higher long-term adherence to the dietary plan compared to CER. Therefore, we also anticipate a major weight and FM loss in IER group, comparing to CER, with a greater retention of FFM, reducing therefore AT [6, 23, 30], due to the inclusion of 7-day breaks to restore EB every 2-weeks of ER, which can minimize the compensatory mechanisms associated with ER and WL, such as changes in appetite-related hormones [24] and some behavioral compensations such as increases in sedentary behavior [26].

During WL phase, we expect to find a reduction in all EE components, as usually seen during ER, namely REE and non-resting EE (spontaneous PA (SPA), non-exercise PA (NEPA), and exercise PA (EPA)) [72].

WL usually causes a reduction in thyroid hormones (T3 and T4), insulin and leptin, increasing appetite [7, 73], and causes an increase in cortisol, which reduces EE [22]. We expect to find a lower reduction in insulin, leptin, thyroid T3 and T4, as well as a lower increase in cortisol in IER, comparing to CER. The minimization of these compensatory adaptations can be explained by the 1-week EB every 2-weeks of ER. After ER intervention, we anticipate a successful WL maintenance in both groups, possibly greater in the IER group, as well as a lower AT.

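### The planned accelerometer intensity categories put sedentary and light activity in one bin, so those variables cannot show a shift from light activity to sitting, a compensation the protocol itself invokes

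*Protocol article*

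**What the plan says.** Section 3.3 of the protocol article (Free-living physical activity and total energy expenditure) commits to reporting "average time at each intensity level (sedentary or light, moderate, hard and very hard PA intensities"). The lowest class is "sedentary or light: <2689 counts per minute", equated with less than 3.00 METs, and the next is "moderate: 2690–6166 counts per minute", equated with 3.00–5.99 METs. The article gives no count threshold between sitting and light activity, no posture measure and no sitting-time questionnaire.

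The same section derives PAEE from the accelerometer by separate published equations and adds it to resting expenditure and the thermic effect of food to give total daily expenditure.

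On the behaviour of interest, the Introduction lists adaptations to negative energy balance "such as increasing sedentary behavior and/or decreasing light PA", and describes them as "more consistently observed in diet-only induced WL". The Discussion confirms that this trial is diet-only. It also gives, as part of the reason for expecting better results with intermittent restriction, that the one-week breaks can reduce "some behavioral compensations such as increases in sedentary behavior".

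**The concern.** The two behaviours that the Introduction pairs as the compensation are the two that section 3.3 pools. A woman who replaces light household or walking activity with sitting during energy restriction has compensated in the sense the protocol describes, yet her time-at-intensity profile is unchanged.

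What is at stake is the mechanistic reading. If the arms differ, or do not differ, in fat loss, the authors will want to say whether behavioural compensation contributed. With the categories as fixed, the intensity variables carry no information on that question in either direction.

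**Working it through.** The plan states no figure here that needs reproducing. The check has three steps.

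**1. Pass count values through the stated cut-points (section 3.3).**

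| Counts per minute | Category under the plan |
|---|---|
| 0 | sedentary or light |
| 50 | sedentary or light |
| 100 | sedentary or light |
| 500 | sedentary or light |
| 1500 | sedentary or light |
| 2500 | sedentary or light |
| 2688 | sedentary or light |
| 2690 | moderate |

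Let *m* minutes per day move from any value in the lower part of that range to any other value below 2689. The change in the lowest category is −*m* + *m* = 0 min/day, and the other three categories are untouched. This holds for every *m*.

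**2. Ask whether a shift that leaves the categories unchanged could matter in energy terms.** The documents give no figures for this, so the following is an illustration on assumed inputs: body mass 90 kg, 1 MET = 1 kcal/kg/h, and a difference between light activity and sitting of 0.5 to 1.0 MET.

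Energy change = (*m*/60) × MET difference × 90 kg

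| Shift (min/day) | At 0.5 MET | At 1.0 MET | Change in any planned category |
|---|---|---|---|
| 30 | 22.5 kcal/d | 45 kcal/d | 0 min/day |
| 60 | 45 kcal/d | 90 kcal/d | 0 min/day |
| 90 | 67.5 kcal/d | 135 kcal/d | 0 min/day |

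For scale only: the Introduction cites adaptive thermogenesis of about 209 kJ/d in the continuous arm of an earlier trial in men, and 209/4.184 ≈ 50 kcal/d. That is a resting-expenditure quantity and is not the same thing as lost activity. The comparison shows only that an hour's shift could be of similar order to an effect the trial cares about.

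**3. Check whether another planned measure fills the gap.** PAEE comes from the same device by different equations, so it may fall when light activity becomes sitting. It is one daily total, however. A fall could equally come from less moderate activity, or from lower body mass where the energy conversion depends on mass. The Discussion lists as a limitation that accelerometry may not capture PAEE accurately. PAEE may therefore register part of the shift but cannot identify it as more sitting.

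**The case against.** The strongest reply is that no planned outcome is damaged. The outcomes and objectives listed in the Abstract, Introduction and Discussion are fat mass, adaptive thermogenesis, weight, fat-free mass, energy expenditure components and hormones. Neither sedentary time nor time at intensity is among them. The sentence about sedentary behaviour in the Discussion is a supporting mechanism, not a hypothesis to be tested. The matching expectation on outcomes is a fall in expenditure components, including spontaneous and non-exercise activity, and PAEE addresses that. The cut-points also follow a cited source, and further exploratory variables could sit in a fuller document. All of this limits the weight of the point. It does not remove it, because section 3.3 actively fixes a pooled class where the rationale needs two.

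Three stronger readings are tempting and should not be drawn.

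- **That the trial as a whole cannot detect the shift.** The documents do not support this, because PAEE may move with it. The limit applies to the time-at-intensity variables.
- **That the plan would lead to a false finding of no compensation in both arms.** Nothing in the article plans such an inference from the categories, and a reader would also have PAEE and total expenditure.
- **That the lowest bin is nearly constant because the women are inactive.** The criterion is "Inactive (less then 150 min/week of moderate PA or 75 min/week of vigorous PA". Taking only the moderate limit, 150/7 = 21.4 min/day, and on a 600-minute valid day (600 − 21.4)/600 = 96.4% of wear time would fall in the bin. This is not a floor. Adding the vigorous limit, 75/7 = 10.7 min/day, gives (600 − 32.1)/600 = 94.6%. Screening is by email, phone and online interview, so it does not cap what the device later records. The plan also reports minutes, not shares, and the minutes in the bin vary with wear time.

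**Conclusion.** The point holds in a limited form. Under the cut-points of section 3.3, the time-at-intensity variables cannot show movement between light activity and sitting: the change is exactly 0 min/day whatever the size of the shift. That follows from the category definitions alone and rests on no assumption. The energy illustration does rest on the assumed body mass and MET difference and should be read only as an order of magnitude.

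The consequence is confined to interpretation of one mechanism. Adaptive thermogenesis is computed from measured and predicted resting expenditure with fat and fat-free mass (section 3.2.1), and the fat-mass comparison uses DXA (section 3.5.1). Neither depends on the intensity categories. This is a worthwhile, inexpensive improvement and not a threat to the primary conclusions.

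**What to change.** Before any outcome data are seen, split the lowest category into sedentary and light at a prespecified and justified lower count threshold, leaving the 2690 boundary and the higher classes as they are. A value of 100 counts/min, with 50–200 as a sensitivity range, could serve as a starting point. These numbers are assumptions and do not come from the article. Report sedentary and light minutes per day, adjusted for wear time, with the group-by-time contrasts already planned in section 3.5. Label them exploratory and set them beside PAEE.

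If the authors prefer to keep the four categories, the alternative is to state that the intensity data will not be used to draw conclusions about sedentary compensation.

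The cost is small. The device already records the counts, so this is reprocessing of existing files with no new visit or measurement. The downsides are that the threshold must be defended and that two further exploratory variables are reported. Fixing the threshold now avoids a choice made after the results are known.
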